#### Cognitive-emotional factors

We will use the standardised and validated Patient-Reported Outcomes Measurement Information System (PROMIS) [73] questionnaires to measure anxiety, depression, cognitive function, self-efficacy, satisfaction social roles and activities, social isolation and social and instrumental support; all known to be impacted in non-specific LBP [74]. As a German version of the PROMIS questionnaire for emotional and instrumental support is not available, a validated German questionnaire [75] will be used for this outcome.

#### Additional musculoskeletal pain locations and cardiovascular risk factors

The presence of other musculoskeletal disease is a known risk factor for non-specific LBP [76] and will be assessed using the Nordic Musculoskeletal Questionnaire [77] which asks for self-report presence of pain in different body regions. Known cardiovascular risk factors for disc herniation (known diabetes, hypertension, high cholesterol and parent who had suffered a myocardial infarction before age 60) will be captured as yes/no response on questionnaires [78].

#### Central sensitisation inventory questionnaire

The Central Sensitisation Inventory questionnaire will assess central sensitisation [79] as a measure of central nervous system hypersensitivity. This tool may be a potential surrogate measure of more time and personnel-costly pain threshold and temporal summation of pain measures. A score of >40 on Part A of the inventory indicates central sensitisation.

#### Demographic and standard outcome measures

We will collect age, occupation (categories per an established taxonomy [80]), weight, height, BMI, smoking history (per the DKFZ-Lymphomstudie [81]), pain duration, pain intensity (visual analogue scale), Oswestry Disability Index, short form of the international physical activity questionnaire [82], Tampa scale for kinesiophobia [83], fear avoidance belief questionnaire [84], current prescription medication, trunk muscle strength [85] and trunk muscle endurance [86]. These measures will characterize the population but not be included in sub-grouping.

### Bias

Project staff conducting the participant testing will be blinded to group status. Should the volunteer reveal their pain status to the operators, the protocol deviation will be noted. Questionnaires will be completed via SoSci (https://www.soscisurvey.de/) and inaccessible to the testers. Data will be encoded by a unique, random, four-digit participant code to blind all steps of analysis.

### Study size

For sub-grouping analyses using machine learning methods, the approach of Foreman [87, 88] to calculate the sample size is used: 2^k^ (where k = number of variables) is minimum sample size and 5*2^k^ is the most conservative sample size. The UK Biobank data study [31, 89] provided only a sub-set of the required parameters, thus the impact of the additional measures in our proposed study (e.g. spine MRI) on sub-grouping is unclear. In this preliminary work [31], less than seven variables were required to characterise a LBP collective, with two specific variables being most important for defining sub-groups. Thus, we argue that using up to 8 variables (2^8^ = 256) across spinal tissue, nervous system and psychosocial domains will likely be sufficient to detect the largest and clinically relevant sub-groups. Therefore, we conservatively target a sample of 300 people with non-specific LBP and 100 controls. This will enable valid subgrouping/classification of patients with non-specific LBP with up to 8 variables in the primary analysis, with additional power for sub-domain analyses with less variables as required. The choice of a 3:1 ratio LBP-to-control was pragmatic for project feasibility and because the focus of our project is on sub-grouping in LBP rather than in pain-free controls.

### Data handling and processing

To promote data quality, questionnaire data entered by the participant and data entered by study staff (e.g. body mass, endurance times) during testing will be collected via SoSci (https://www.soscisurvey.de/). Monthly back-ups of these data from SoSci will be performed during the data collection process onto the servers of the Hochschule für Gesundheit or the Hochschulnetz NRW (“sciebo”). Any events or protocol deviations during testing will be noted in free-text format in the same system. Where feasible, automatic range checking will be implemented during data entry onto SoSci and will be implemented as part of data processing. Where team staff members are not priorly experienced in the outcome measures, training will be provided by experienced team members and/or collaborators along with standard operating procedure documentation. As part of standard practice, MR image data is checked visually by the MR-operator and investigator team member during scanning and scans repeated once if, for example, movement or other artefacts impact the images collected. MR images are measured manually by trained staff using established protocols [48, 49, 90] to obtain the numerical outcomes of interest. The remaining numerical data (e.g. objective physical activity measures, strength, endurance, body mass) will be collected per established standard protocols. A tabulated list of the outcomes is contained in Table 1.

For the data-science approaches implemented, complete data is required. Therefore, missing data will be imputed. The exact method of data imputation will be determined in consultation with a biostatistician once the degree of missingness is known and whether data are “missing-at-random” or not. We anticipate the missingness will be small, as we are performing a cross-sectional study and not a test-retest design, such as in a randomised controlled trial where dropouts inevitably occur. Additional sensitivity analyses performed to assess impact on the findings.

### Analytical and statistical methods

The following approach, based on our preliminary work [31, 47], will be used (see also Fig 1).

**Fig 1 pone.0282346.g001:**
[figure not shown]
Approach to artificial intelligence tool implementation. GOÄ: Gebührenordnung für Ärzte (German medical cost database).

Dimensionality reduction will be performed to identify the most relevant variables (of those listed; Table 1) for subgrouping and classification. Given known challenges with data-analytic variable weighting and multidimensional data (e.g. scaling each variable to 0–1) [31], our first step in dimensionality reduction will focus on traditional statistical methods including paired t-tests, analysis of covariance and multicollinearity assessment through correlation analysis [31]. Following this, pending the number of important variables (e.g. if more than 8 variables remain) we will consider variable weighting using a decision tree classifier and targeted projection pursuit with artificial neural networks [91]. The outputs will be used to select the most relevant variables distinguishing non-specific LBP from controls (2-class model).Following determination of the most important variables, pain-free controls will be removed from the data for the following clustering steps. Cluster validation methods [92], including Calinski-Harabasz, Davies-Bouldin and Sillouette values, will be used to determine the optimal number of clusters and variables for the remaining non-specific LBP data. Given the potential for high dimensionality introducing noise and influencing clustering, we will evaluate the outputs of clustering using all outcomes and within individual domains (e.g. in preliminary work [31, 47], psychological and brain MRI variables correlated more highly with each other within their domains than between variable domains). The output of this step will allow us to determine the optimal number of clusters and variables.Based on the information in step B, we will apply fuzzy c-means clustering model [31] of non-specific LBP on either the primary clustering or domain specific clustering. The clusters derived in this step will be used to label classes of non-specific LBP.Outputs from steps B and C in terms of class labels will be used to evaluate non-specific LBP classification. We will apply Support Vector Machine, Naïve Bayes, k-Nearest Neighbour and Random Forest binary/multiclass classifiers as appropriate for the data. Given we are focusing on internal (i.e. on the current dataset, rather than a second newly collected dataset from a different research centre or project) validation of a classification model, validation of the model will be done via k-fold cross validation, as random data-splitting is not generally recommended for internal model validation [93–96]. The output of this will be a sub-grouping tool for people with non-specific LBP assuming availability of all data and tests and no consideration of test cost.We will consider the following sensitivity analyses:

we will evaluate random data-splitting and repeat steps B and C to determine if the clustering outputs hold across random samples;we will apply steps B to E within each domain (e.g. brain MRI, psychosocial variables, spine MRI) as required;repetition of analysis only with participants without any imputed data; to examine the potential impact of missing data.consideration of impact of secondary variables (see bottom panel of Table 1) on sub-grouping.the methods of step (D) will be reapplied under constrained cost assumptions, considering financial-cost, time, and patient burden of obtaining each clinical outcome. Financial costs will be according to current rates according to the Gebührenordnung für Ärzte; time will be according to clinical measure and patient burden will be according to an ordinal scale. The output will be a model for most effective sub-group identification for people with non-specific LBP respecting cost/time/burden constraints.consider the findings of sub-grouping when patients with or without radiological evidence of degenerative changes (see Quantitative variables and data collection > Spine MRI) are included.

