Known clinical diagnosis of non-degenerative specific spinal conditions: cancer, vertebral fracture, vertebral or intervertebral disc infection or inflammatory spondyloarthropathy.Known clinical diagnosis of spinal nervous system damage: cauda equina, spinal stenosis [41] or diagnosed radiculopathy [42] as defined in prior work. Leg/radiating pain is not an exclusion criterion, nor is spinal stenosis or foraminal stenosis on imaging with no neurological damage.Known clinical diagnosis of severe degenerative spinal conditions: grade IV spondylolisthesis, severe deformity (e.g. hemivertebrae, scoliosis > 50 degrees) requiring more than two prior medical specialist consultations.Previous spine surgery (being on a waiting list for surgery is, of itself, not an exclusion).Prior major head trauma or brain surgery.Known clinical diagnoses of the following neurological conditions: cerebral palsy, dementia, epilepsy, motor neurone disease, multiple sclerosis, Parkinson’s disease, spinal muscular atrophy, stroke, polyneuropathy.Known major psychiatric disorder: mania, bipolar affective disorder, major depressive disorder, severe personality disorder, severe anxiety disorder, severe obsessive-compulsive disorder [43] as these may impact brain MRI measures [44].Current pregnancy or up to 6 months post-pregnancy (pelvic girdle pain associated with pregnancy typically resolves in ~80% of women by 6 months post-partum [45, 46]).Any further absolute contraindications for brain or spine MRI (e.g. cardiac pacemakers, metal implants and foreign bodies, middle ear implants, drug pumps, electronic stimulation devices).

For the pain-free control group, the following additional exclusion criteria will be applied:

current spinal (neck, upper back, or low back) pain impacting function (self-report),LBP lasting for more than 24 hours within the last year (except for muscle soreness related to physical activity or exercise),previously, at any point, missed days from work due to LBP,previously, at any time, consulted a health professional for the treatment of LBP (e.g. physiotherapist and general practitioner).

Pain-free controls will be matched to LBP participants on a 1:3 basis (see Sample Size section for rationale) by

sex (male or female)age brackets (18-25yr, 26–3, 36-45yr, 46-55yr)height (±5 cm; as body height has an impact on spine morphology)additionally, where possible, a body mass index of ±5 kg/m^2^ will be preferred.

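### Step A screens variables with paired t-tests, but controls are matched 1:3 and the protocol does not say how pairs are formed

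*Protocol article*

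**What the plan says.** Under Participants the protocol states: "Pain-free controls will be matched to LBP participants on a 1:3 basis". The matching factors are sex, age bracket and height, with BMI where possible. Study size gives the numbers, "we conservatively target a sample of 300 people with non-specific LBP and 100 controls", and adds: "The choice of a 3:1 ratio LBP-to-control was pragmatic for project feasibility".

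Step A of Analytical and statistical methods then describes the first step of dimensionality reduction as "traditional statistical methods including paired t-tests, analysis of covariance and multicollinearity assessment through correlation analysis". Its purpose is stated as follows: "The outputs will be used to select the most relevant variables distinguishing non-specific LBP from controls (2-class model". If too many variables remain, for example more than 8, a decision-tree classifier and targeted projection pursuit will be considered. Controls are then removed, and cluster validation and clustering proceed on LBP participants only.

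The protocol does not say how a set of one control and three LBP participants becomes a pair. It mentions neither averaging within sets, nor dropping participants, nor a mixed or conditional model. It gives no alpha, effect size or power for this step.

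**The concern.** The test named does not fit the design as written. The contrast is between LBP participants and controls, so a pair can only mean a matched pair of different people. Within-person pairing is ruled out, because Data handling and processing describes the study as cross-sectional and not test-retest. Matched sets of 1 + 3 do not supply one-to-one pairs without a further rule.

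Two obvious improvised rules both do damage. Keeping one patient per control loses precision, so real differences are more easily missed. Pairing each control with all three of its patients and treating the 300 differences as independent understates the standard error, so noise variables pass more easily. Step A feeds the choice of clustering variables, and Study size budgets for only up to 8 of them. If the pairing rule were settled after the group data are seen, it would also be a data-dependent choice made ahead of the clustering.

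**Working it through.** **The plan's own figures.** Study size uses 2^k with k = 8: 2^8 = 256, which reproduces. The 3:1 split also reproduces: 300/3 = 100. There is no test-level figure to reproduce.

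**Inputs.** From the protocol: 300 LBP participants, 100 controls, 1:3 matching. Assumed, because the protocol is silent: two-sided alpha 0.05, a difference of 0.3 SD, equal SD in both groups, complete sets of 1 + 3, and within-set correlation ρ between 0 and 0.5.

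**Variance of the estimated group difference, in SD² units.**
- One patient per control, 100 pairs: 2(1−ρ)/100.
- Mean of three patients minus their control, 100 sets: (1 + 1/3)(1−ρ)/100 = (4/3)(1−ρ)/100.
- Relative efficiency of the first to the second: (4/3)/2 = 0.67, for any ρ.
- At ρ = 0 the standard errors are √(2/100) = 0.141 and √(1/300 + 1/100) = 0.115, a ratio of 1.22.

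**Power at a 0.3 SD difference.** The normal approximation for independent groups gives 56.4% for 100 v 100 and 73.8% for 100 v 300. Simulation of the matched sets (20,000 runs per setting) gives:

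| ρ | One patient per control | Set-level difference, all 400 |
|---|---|---|
| 0 | 55.4% | 73.2% |
| 0.1 | 60.6% | 77.7% |
| 0.3 | 70.6% | 86.7% |
| 0.5 | 84.8% | 95.6% |

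The loss is about 18 percentage points at ρ = 0 and about 11 at ρ = 0.5.

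**Type I error if each control is reused three times.** Treating the 300 differences as independent gives a nominal variance of 2(1−ρ)/300. The true variance is (4/3)(1−ρ)/100 = 4(1−ρ)/300. The ratio is 2 whatever ρ is, so the standard error is too small by √2. Real two-sided error at nominal 5%: 2[1 − Φ(1.96/√2)] = 2[1 − Φ(1.386)] = 0.166. Simulation gives 0.162 to 0.167 over ρ = 0 to 0.5.

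**Type I error of the alternatives (simulation).**
- One patient per control: 0.049 to 0.050.
- Set-level differences: 0.048 to 0.051, with all 300 LBP participants used.
- Unpaired t-test on 300 v 100, ignoring the sets: 0.050 at ρ = 0, falling to 0.018 at ρ = 0.3 and 0.006 at ρ = 0.5. Simply dropping the pairing is therefore not a neutral repair.

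**Illustration of scale.** By count, Table 1 lists at least 44 single-valued candidates before any connectivity measure: 16 spine MRI, 12 grey-matter volumes, 8 sensory or laser, 8 questionnaire. If half were null (an assumption), a 5% screen would pass 22 × 0.05 ≈ 1 of them by chance and a 16.6% screen 22 × 0.166 ≈ 4, against a budget of up to 8 variables.

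**The case against.** Several points can fairly be made for the plan.

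- **A paired analysis can be made to fit.** A reader might infer that paired t-tests must either discard 200 patients or reuse the controls. That is not so: a test on the mean of three patients minus their control keeps everyone and holds the error rate. This stands. It leaves a mismatch that the text does not resolve, not a design that cannot be analysed.
- **Neither harmful procedure is written down.** The protocol says neither that it will drop participants nor that it will reuse controls. This also stands, and the figures above show what the wording permits, not what is planned.
- **The t-test is not the sole gate.** A reader might infer that it alone decides which variables reach clustering. The list is open, ANCOVA is on it and can use all 400 participants, and further weighting and cluster validation may follow. This stands, with two limits: no rule says which method prevails when they disagree, and the later weighting is only to be considered.
- **No error rate is promised.** The step is exploratory, so 16.6% does not breach a stated 5%. This stands.
- **Detail may sit in a fuller plan or in the cited preliminary work.** This is the weakest objection. How pairs are formed could be left to such a document, but the protocol positively names a method that does not match its own stated ratio.

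**Conclusion.** The point holds as a mismatch between a named test and the stated design: paired t-tests for 1:3 matched sets, with no rule for forming pairs. Depending on how the gap is filled, the cost ranges from none (set-level differences), through a one-third loss of efficiency (power 56% v 74% at ρ = 0, 85% v 96% at ρ = 0.5), to a nominal 5% screen running at about 16.6%. The power figures depend on the assumed 0.3 SD effect, alpha and ρ; the 16.6% depends on the nominal 5% and on complete sets, but not on ρ.

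The consequence is less reliable screening of variables. The documents do not support calling it a breach of a stated error rate, or saying that this test alone determines the clusters. Severity is should-fix, not must-fix.

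**What to change.** In step A, replace the paired t-tests with a test that respects the 1:3 sets and uses all 400 participants. Either of these will do:

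1. A one-sample t-test on 100 set-level differences, each being the mean of the three matched LBP participants minus their control. This is the simplest option and needs no covariates.
2. A linear mixed model with group as fixed effect and matched set as random intercept. This copes more easily with incomplete sets. The ANCOVA already named, adjusted for the matching factors, is an acceptable substitute.

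If the ANCOVA route is taken, add a clause to reconcile it with Table 1, which reserves age, sex and BMI for secondary analyses: they would enter here only as adjustment for the matching, not as candidate variables for sub-grouping.

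The cost is one sentence in step A, with no new data. The sentence should be fixed before any group comparison is run.

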Multiple domains impact a person experience of pain [12, 13]. In non-specific LBP, damage to the spinal tissues (nociceptive pain drivers), alterations in the processing of the pain signal (nervous system dysfunction), presence of other musculoskeletal diseases (comorbidity drivers), negative mood/affect, poor self-efficacy, and the use of maladaptive coping strategies (cognitive-emotional drivers) can influence the pain experience [6–9, 13]. Further, abnormal central pain processing including central sensitisation [14, 15], reorganisation of (sub)cortical brain pathways [16], and changes in brain connectivity [17–19] can contribute to pain. Beliefs, fear of movement, depressive symptoms, anxiety, past experiences, self-efficacy, presence of other painful conditions may mediate the non-specific LBP experience [20, 21].

Of the known factors which may contribute to an individual’s experience of non-specific LBP, there is not a single one that can differentiate between those who have non-specific LBP and those who are pain free [22]. In a recent systematic review with multivariate meta-analysis [23] we showed that multiple domains are impacted in LBP and that there was only one primary study [24], of small sample size (n = 32) which considered more than two domains of central nervous system adaptation, tissue changes and/or psychological factors.

Artificial intelligence (AI) and machine learning offer automated methods to detect unique sub-groups that ‘explain’ the presence and characteristics of a disease [25, 26]. AI techniques have been used in other diseases (e.g. severe sepsis [27], cardiovascular disease [28], diabetes [29]) to improve clinical outcomes. A systematic review of AI applications in LBP [30] noted that (a) no studies to date considered if possible sub-groups exist, (b) a limited number of body systems were evaluated and (c) sample sizes remained small (ranging from 24 to 171 participants in these studies). There is an evidence gap for a study to use data-science techniques in LBP in an appropriate sample size. Since this review, work from our group [31], using data from the UK Biobank, showed that sub-groups could be derived in (chronic) LBP on the basis of psychosocial variables and then accurately classified, but the data set lacked spinal tissue and pain sensitisation measures and key clinical data (e.g. pain intensity, disability and pain duration).

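### Step A picks the sub-grouping variables by the LBP-versus-control contrast, so it can drop markers of minority or opposite-direction sub-groups within LBP

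*Protocol article*

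**What the plan says.** All of this is in the Protocol article, Analytical and statistical methods, unless noted.

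- Purpose of step A: "Dimensionality reduction will be performed to identify the most relevant variables (of those listed; Table 1) for subgrouping and classification".
- First stage: "our first step in dimensionality reduction will focus on traditional statistical methods including paired t-tests, analysis of covariance and multicollinearity assessment through correlation analysis".
- Second stage, conditional on how many variables remain (more than 8 is the example given): "we will consider variable weighting using a decision tree classifier and targeted projection pursuit with artificial neural networks".
- Criterion: "The outputs will be used to select the most relevant variables distinguishing non-specific LBP from controls (2-class model".
- Then "pain-free controls will be removed from the data for the following clustering steps".
- Step B applies cluster-validity indices to the LBP data to settle the number of clusters and the variables, and adds that "we will evaluate the outputs of clustering using all outcomes and within individual domains". Step C fits fuzzy c-means on that basis and supplies the class labels.
- The sensitivity analyses repeat steps B and C on random splits, and "we will apply steps B to E within each domain (e.g. brain MRI, psychosocial variables, spine MRI) as required". They also cover participants without imputed data, the secondary variables, cost constraints and radiological degeneration. None is stated to run without the step A screen.

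Study size caps the primary analysis at 8 variables across three domains. The Introduction remarks that, among known factors, "there is not a single one that can differentiate between those who have non-specific LBP and those who are pain free".

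**The concern.** The filter and the target are different contrasts. Step A rewards a variable for separating the LBP group as a whole from controls. Clustering needs variables that separate LBP participants from each other. The two can disagree in three ways:

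- A variable abnormal in only one sub-group has its LBP-control mean difference diluted by that sub-group's share.
- Where sub-groups deviate in opposite directions, the mean difference can vanish.
- A variable shifted equally in everyone with LBP passes easily but says nothing about sub-groups, and it uses one of at most 8 places.

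What is at stake is the reading of a null result. The Discussion says that finding no relevant sub-groups would strengthen the case for current generic management. If the screen had removed the variables that carry the sub-groups, that conclusion would come from the selection step and not from the patients.

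**Working it through.** **Inputs from the protocol (Study size).** 300 LBP, 100 controls, up to 8 variables. The plan's own figure reproduces: 2^8 = 256, and the target of 300 exceeds it. This only fixes the cap of 8. It says nothing about which 8 variables are chosen.

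**Assumptions, since step A gives none.** Two-sided alpha 0.05 (with 0.05/60 as a strict variant), within-group SD of 1, shifts in SD units, and groups treated as independent. The protocol plans paired tests on 1:3 matched sets but gives no within-set correlation.

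**Formula.** If a share f of LBP is shifted by s and the rest are like controls:

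- mean difference = f·s
- LBP variance = 1 + f(1−f)s²
- SE = √(1/100 + LBP variance/300)
- chance of being kept = Φ(z − 1.96) + Φ(−z − 1.96), with z = mean difference/SE

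**Worked case, f = 0.2, s = 1.** Difference 0.20; variance 1 + 0.16 = 1.16; SE = √(0.01 + 0.003867) = 0.1178; z = 1.70; chance kept = 0.397.

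| Pattern in LBP | Mean difference | LBP SD | Kept at 0.05 | Kept at 0.05/60 |
|---|---|---|---|---|
| 10% at +1 SD | 0.10 | 1.044 | 14% | 0.6% |
| 20% at +1 SD | 0.20 | 1.077 | 40% | 5% |
| 30% at +1 SD | 0.30 | 1.100 | 72% | 21% |
| 50% at +1 SD | 0.50 | 1.118 | 99% | 81% |
| 50% at +1, 50% at −1 SD | 0 | 1.414 | 5% | 0.1% |
| 30% at +1, 70% at −0.43 SD | 0 | 1.195 | 5% | 0.1% |
| All at +0.5 SD (no sub-groups) | 0.50 | 1.000 | 99% | 84% |

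The 5% in the cancelling rows is only the false-positive rate. In simulation with a fixed 50:50 split at ±1.5 SD it was 1.4%, both with a Welch test and with a paired test on 1:3 set means (2,000 runs). A 20% sub-group at 1 SD was kept in 42% of simulated runs, in line with the 40% above.

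**Effect on clustering in an unfavourable case (300 runs).** Four variables were shifted +0.5 SD in all LBP and four were at ±1 SD in two equal sub-groups. Fuzzy c-means with two clusters was run on variables scaled 0–1. The 5% screen kept on average 3.96 of the four uninformative variables and 0.12 of the four sub-group variables, and it kept none of the latter in 89% of runs. The adjusted Rand index against the true sub-groups was 0.03 after the screen, 0.90 with all eight variables unscreened, and 0.91 with the four sub-group variables only.

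**Dependence on the scenario.** Take 54 candidates, six of them marking a 20% sub-group at 1.5 SD, and keep the top 8 by t-statistic. With eight competing variables shifted 0.4 SD in all LBP, about 2.1 of the six survive. With four competitors about 3.5 survive, and with none about 4.7. The loss is therefore not a fixed quantity.

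**The case against.** The strongest reply has four parts.

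1. *Step B already selects variables within LBP.* This stands in part. The validity indices can discard uniformly shifted variables that add no structure. They cannot restore variables that never reach step B.
2. *The mention of all outcomes may mean all of Table 1.* This is a fair reading. Data handling and processing refers to Table 1 as the list of outcomes, and worry about high dimensionality fits poorly with 8 or fewer variables. But the sentence follows the selection and does not say that discarded variables return. The text does not settle it.
3. *The decision tree and projection pursuit can respond to more than means.* They are only to be considered, they follow the mean-based stage, and they are aimed at the same two-class target.
4. *The control contrast is a relevance filter.* This stands. Table 1 includes raw disc, muscle and grey-matter volumes, and Participants notes that height affects spine morphology. Selection purely within LBP could yield clusters of sex or body size.

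Two stronger readings are tempting and not supported. A reader might infer that step A removes sub-group variables in general. It does not: a one-directional shift in half of LBP is kept about 99% of the time, and 30% of LBP at 1.5 SD about 96%. The Discussion also says that the study aims at the largest sub-groups and accepts that smaller ones may be missed, though it gives no share. A reader might also take the Introduction's remark that "there is not a single one that can differentiate between those who have non-specific LBP and those who are pain free" as an admission that the screen must fail. That remark is about one factor separating individuals. It does not imply zero mean differences, and the same section says that several domains are affected in LBP.

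**Conclusion.** The concern holds in a limited form. The protocol states a selection rule whose target is LBP versus control, while the study's target is heterogeneity within LBP. The rule can lose markers of a minority sub-group (kept about 14% of the time at a 10% share and 40% at 20%, for a 1 SD shift) and nearly always loses markers whose deviations cancel (at most about 5%). It readily keeps uniform shifts that carry no sub-group information (about 99% at 0.5 SD). Large sub-groups that deviate in one direction are mostly safe.

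These figures rest on an assumed 5% threshold, unit SDs and independent groups. A stricter threshold makes the loss worse; larger shifts or shares make it smaller. The effect on the final clusters depends on how many uniformly shifted variables compete for the 8 places, which cannot be known in advance. If step B is in fact meant to run on all of Table 1, much of the concern is met, but the protocol would need to say so.

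**What to change.** State that steps B and C are also run on the primary Table 1 variables without the LBP-versus-control screen. Apply the correlation filter first. Then choose variables inside the LBP group, by the step B validity indices or by sparse-clustering weights, within the cap of 8 and with all three domains represented. Say explicitly what the step B reference to all outcomes covers.

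Compare these clusters with those from the two-class selection and report both. Do not conclude that sub-groups are absent from the screened analysis alone. Use the controls afterwards, to describe each cluster's profile as a deviation from pain-free people.

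No new data are needed. The costs are extra analysis work and a second set of clusters to interpret. Some retained variables will not differ on average from controls, and unscreened clusters may reflect sex or body size. Size-dependent measures should therefore be adjusted for sex, age and height before clustering, or the clusters checked against those characteristics.
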